## **6.8 Cross Over**

Cross-over into the experimental arm is intended for patients randomized into the standard arm if the following criteria is met:

- Starting from day 10 after randomization
- No improvement or worsening of clinical condition

For cross-over, all inclusion / exclusion criteria (except mechanical ventilation/ECMO) must again be met as specified in Sections 5.3 and 5.4.

The actual possibility for cross-over into the experimental arm is based on discussion with the coordinating investigator on a case-by-case decision.

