### **7.3.3 Laboratory parameters**

Nose/throat swabs are collected at day 0 and day 1 (before first CP administration) and subsequently at day 2, 3, 5, 7, 10, 14, 28 or until discharge. Serum for SARS-Cov-2 diagnostic is collected at baseline and subsequently at day 3, 7, 14 and once during the follow-up period (between day 35 and day 84). Serum collection on the following days is optional: day 1, 2, 3, 10 and 28. Details on sample collection and schedule will be provided in the laboratory manual.

Nasopharyngeal swabs are analysed for SARS-CoV-2 RNA viral load by semi-quantitative real-time RT-PCR in the laboratory of Prof. [name] (Center for Infectious diseases, University Hospital Heidelberg). Patient serum obtained at the different time points is stored

at -20° C until further use. Antibodies directed against SARS-CoV-2 are going to be analysed in recipient serum before (day1) and after (day 3) treatment. IgG Antibodies are detected in standard ELISA tests. Further, analyses for neutralizing antibodies are performed by [name]. [name] (DKFZ, Heidelberg). Cytokine analyses is performed in the laboratory of PD [name] (NCT Heidelberg) with the Bio-Plex Pro Human Cytokine 48-Plex Screening Panel (Biorad, Munich, Germany). To evaluate the effects of CP onto inflammation and cytokine levels, a first analysis is performed after the first randomized 40 patients. All other serum specimens are analyzed at the end of trial.

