## 10.4 Analysis Populations

### 10.4.1 Full Analysis Population

The Full Analysis Population (FAP) includes all randomised patients with treatment groups assigned in accordance with the randomisation, regardless of the treatment actually received. Patients who were randomised but did not subsequently receive treatment are included in the Full analysis population. The analysis of data using the Full analysis population therefore follows the Intention-to-Treat principles (ITT).

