#### **10.5.5 Analysis of the Secondary Endpoints**

Overall survival is analyzed by using a Cox regression model adjusting for treatment and patient group, determining hazard ratios with 95% confidence intervals and (descriptive) p-values. Survival estimates are calculated using the Kaplan-Meier method together with 95% log-log-type confidence bands, and the 28-day survival rate will be given for both treatment groups together with 95% confidence intervals. Analogously as for the supplementary analysis of the primary endpoint, an IPCW model and a RPSFT model will additionally be fitted for the secondary endpoint overall survival to assess the potential treatment effect in case patients had not switched from the control to the experimental arm.

Time until discharge will be assessed similarly to the primary endpoint, providing Kaplan-Meier estimates for the cumulative discharge rate for both treatment groups and conducting a log-rank test stratified for the factor “patient group”, and censoring patients who died from any cause at day 84 in analogy to the analysis of the primary endpoint. Analogously as for the sensitivity analysis of the primary endpoint, an IPCW and a RPSFT model will additionally be fitted for the secondary endpoint ‘time until discharge’ to assess the potential treatment effect in case patients had not switched from the control to the experimental arm.

The secondary endpoint “requirement of mechanical ventilation (yes/no)” is analyzed by means of a logistic regression model adjusting for the factors treatment and patient group. Also, absolute and relative frequencies will be given for this endpoint, together with 95% confidence intervals.

The secondary endpoints SARS-CoV-2 viral load and antibody titres will be assessed over time by means of linear mixed models adjusting for treatment group, patient group, and

baseline value as fixed factors, as well as time as repeated factor using an unstructured covariance matrix, calculating least square means estimates and 95% confidence intervals.

While it is indirectly assumed by these models that data will be missing at random, i.e. that the missingness can be explained by observed covariate and outcome values, we will assess the robustness of this assumption by means of sensitivity analyses by means of pattern mixture models assuming that data will be not missing at random.

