For all secondary endpoints, the analysis will be conducted based on the FAS and as a sensitivity analysis based on the per protocol population.

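### Late between-arm contrasts in viral load and antibody titres are diluted by crossover plasma counted in the standard arm, and these endpoints have no analysis that allows for the switch

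*Protocol*

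**What the plan says.** Protocol 10.5.5 gives the method for both endpoints: "The secondary endpoints SARS-CoV-2 viral load and antibody titres will be assessed over time by means of linear mixed models". The fixed factors are treatment group, patient group and "baseline value as fixed factors, as well as time as repeated factor using an unstructured covariance matrix". No treatment-by-time term and no term for crossover is listed.

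The analysis set is fixed in the same section: "For all secondary endpoints, the analysis will be conducted based on the FAS and as a sensitivity analysis based on the per protocol population". Section 10.4.1 defines the full analysis population as all randomised patients "with treatment groups assigned in accordance with the randomisation, regardless of the treatment actually received".

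Section 6.8 opens crossover to standard-arm patients "Starting from day 10 after randomization" if they have not improved or have worsened. They must meet the eligibility criteria again (ventilation/ECMO excepted), and each case is decided with the coordinating investigator. No expected crossover rate is given. Footnote 13 of the trial schedule restarts the visit schedule at day 1 after crossover.

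Elsewhere the switch is dealt with. Section 10.5.4 plans IPCW and RPSFT analyses for the primary endpoint. In 10.5.5, "an IPCW model and a RPSFT model will additionally be fitted for the secondary endpoint overall survival", and the same is planned for time until discharge. Section 10.4.3 evaluates crossed-over patients in the experimental arm from day 10 for safety.

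On sampling, section 7.3.3 states: "Serum for SARS-Cov-2 diagnostic is collected at baseline and subsequently at day 3, 7, 14 and once during the follow-up period", the last of these between day 35 and day 84. Swabs are due on days 1, 2, 3, 5, 7, 10, 14 and 28, or until discharge.

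**The concern.** A standard-arm patient who crosses over receives plasma containing the antibody that the titre endpoint measures. As 10.5.5 and 10.4.1 read together, later values from that patient still count towards the standard arm. The arms then move together after day 10 for a reason unrelated to the durability of the plasma effect, and a lasting difference could be read as transient or absent.

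Section 10.3 accepts the switch because late plasma should have no major effect on the median time to improvement. That is an argument about a clinical event time. It says nothing about a titre, which infused antibody can raise whenever it is given. Yet these are the endpoints on which a mechanistic reading of the trial would rest, and the switch-adjusted analyses provided for the other time-to-event endpoints are not extended to them.

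**Working it through.** **1. The plan's own model.** The protocol states no figure for the viral load or titre models, so I first checked that its event-time model is read correctly.
- Schoenfeld events for HR 1.6, two-sided 5%, 80% power: 4 × (1.960 + 0.842)² / (ln 1.6)² = 142.1. The plan states 142.
- Control hazard from the 16-day median: ln 2 / 16 = 0.0433. Experimental hazard: 0.0433 × 1.6 = 0.0693.
- Event probability by day 38: 0.807 and 0.928, mean 0.868. Then 142.1 / 0.868 = 163.8, so 164 patients.
- Per arm, 82 / 0.95 rounds up to 87, so 174 in total. The plan's figures reproduce.

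**2. How many controls could cross over.**
- Not improved by day 10: exp(−0.0433 × 10) = 0.648, or 0.648 × 87 ≈ 56 patients.
- Alive at day 10, assuming death is independent of improvement with 20% risk by day 38: 0.8^(10/38) = 0.943.
- Alive and unimproved: 0.648 × 0.943 = 0.611, or about 53 of 87.

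Leaving aside patients who improve and later relapse, 61% is a ceiling. It still includes one-point improvers, patients who no longer meet the criteria and cases not approved.

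**3. Which samples are exposed.**

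| | Before crossover can act | After day 10 |
|---|---|---|
| Required post-baseline serum | days 3, 7 | day 14, one in days 35–84 (2 of 4) |
| Swabs after day 1 | days 2, 3, 5, 7, 10 | days 14, 28 (2 of 7) |

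**4. Dilution.** Let f be the share of sampled controls who have received plasma. Assume that late plasma shifts the outcome as much as early plasma. A late mean difference then keeps (1 − f) of its size. For scale, take a late contrast that would have 80% power with 82 per arm, d = 2.802 × √(2/82) = 0.4375 SD, with control-arm variance increased by f(1 − f)d².

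| f | Late contrast kept | Power | Equal-weight average kept, serum (2 + 2(1−f))/4 | Same, swabs (5 + 2(1−f))/7 |
|---|---|---|---|---|
| 0.20 | 80% | 60% | 90% | 94% |
| 0.40 | 60% | 38% | 80% | 89% |
| 0.61 | 39% | 19% | 70% | 83% |

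The last two columns apply if a single treatment effect is pooled over time, as the listed factors would allow.

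Swabs stop at discharge, so controls still sampled on days 14 and 28 are largely those who could have crossed over. Among them f may exceed the 61% that applies to all controls.

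**5. The clock.** If a control is infused on day 10, the restarted day 3 is original day 12 and the restarted day 7 is original day 16. Section 10.5.5 does not say which clock the model uses. Under the restarted one, plasma-exposed control samples would carry early visit labels, and the early contrasts would no longer be clean.

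**The case against.** A reader might infer that from day 10 the comparison is plasma against plasma. The documents do not support that. Crossover is limited to patients who do not improve or who worsen, requires eligibility to be met again, and is decided case by case. Only f = 100% among sampled controls would empty the contrast, and the protocol gives no rate. Nor can 65% or 61% be read as an expected crossover share.

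A reader might also infer that the mechanism goes untested. It does not: serum on days 3 and 7 and swabs to day 10 precede any crossover effect, section 7.3.3 plans antibody measurement before (day 1) and after (day 3) treatment, and the secondary-endpoints section adds exploratory paired before–after tests.

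The equal-effect assumption is doubtful for viral load, since the protocol itself expects plasma to work better when given early. Analysis by randomised arm is a legitimate treatment-policy estimand, and section 10.5.1 leaves detail to the SAP, which is not shown. Setting post-switch values to missing has its own bias, because switching follows clinical course and the mixed model does not condition on the ordinal scale. All of this stands. It limits the size of the point and argues against replacing the main model.

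It does not remove the gap. The protocol names switch-adjusted analyses endpoint by endpoint and omits these two, and its stated reason does not reach antibody titre. The per-protocol analysis is no assured remedy: permitted crossover is not in itself a deviation, and the exclusions are left to the SAP.

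**Conclusion.** The point holds as dilution of the late contrasts, not as loss of the comparison. As written, values after crossover plasma count in the standard arm, and treatment policy is the only between-arm estimand stated for viral load and antibody titres apart from the per-protocol sensitivity analysis. Serum on day 14 and in days 35–84, and swabs on days 14 and 28, are affected. They keep about 80%, 60% and 39% of the contrast at crossover shares of 20%, 40% and 61%. This rests on an equal effect of late and early plasma, on the protocol's exponential model with a 16-day median, and, for the 61% ceiling, on independent mortality of 20% by day 38. Earlier points are unaffected provided that model time runs from randomisation. The primary analysis is not touched.

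**What to change.** In 10.5.5:

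1. Keep the randomised-arm model in the full analysis set and label it the treatment-policy analysis.
2. State that model time runs from randomisation, not from the schedule restarted after crossover. The original schedule needs the same statement: footnote 1 times visits from the first infusion, which section 6.6 allows up to 7 days after randomisation.
3. Include a treatment-by-time term, and pre-specify the contrasts up to day 10, from samples taken before any crossover infusion, as the crossover-free between-arm comparison.
4. Add a supplementary model that sets values after a standard-arm patient's first plasma infusion to missing. Consider the ordinal scale as a predictor of switching, and apply the planned pattern-mixture sensitivity analysis.

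The cost is analysis wording and programming; no data collection or patient management changes. The downside is fewer late control samples in the supplementary model, with missingness that depends on clinical course. That is why it should supplement the treatment-policy model and not replace it.

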### **Safety Analysis**

The assessment of safety is based mainly on the frequency of adverse events and on the number of laboratory values that fall outside of pre-determined ranges and/or show prominent worsening from baseline during the study phase. Safety analysis is based on the safety population. Adverse events are summarized by presenting the number and percentage of patients having any adverse events or serious adverse events, and having each individual adverse event, and by determining and summarizing the maximum individual toxicity grade (over all forms of toxicity). Furthermore, the most common AEs (those occurring in at least 10% of the treatment group) are determined. Any other information collected (e.g. severity or relatedness to study drug) are summarized as appropriate. Laboratory data are summarized by presenting summary statistics of raw data and change from baseline values. Incidence rates are summarized along with two-sided Clopper-Pearson 95% confidence intervals and analyzed by (descriptive) chi-squared tests.

### **Other Analyses**

- Patients' disposition and reasons for ending the study are presented in frequency distribution tables and individual data listing.

Individual data are presented in listings.

#### **10.5.6 Handling of Missing Data**

For patients with incomplete follow-up, time to last follow-up date is used as the censoring time in the analysis of time-to-event data. Missing data of continuous outcomes over time will be handled via the multi-level approach making the implicit assumption that data are missing at random, thus not requiring any direct imputation of missing continuous data. The robustness of this assumption will be explored in sensitivity analyses by means of pattern mixture models assuming that data are not missing at random. Otherwise, no imputation of missing data will be conducted.

## **11 Data Management**

### **11.1 Data Collection**

As used in this protocol, the term Case Report Form (CRF) should be understood to refer either to a paper form or an electronic data record or both, depending on the data collection method used in this trial.

The data collection will be performed using an eCRF in accordance with the German Corona Consensus Data Set (GECCO).

Data collection using the eCRF can only be done by authorized persons. All study data are password-protected. The eCRF provides several checks for completeness and consistency. Each entry or change of data is tracked with name and exact date. When data has been entered, reviewed, edited and Source Data Verification (SDV) performed, the investigator is

notified to sign the CRF electronically as per agreed project process. A copy of the electronic-CRF will be archived at the study site.

All findings including clinical and laboratory data are documented by the investigator or an authorized member of the study team in the patient's medical record and in the case report form (CRF). The investigator is responsible for ensuring that all sections of the CRF are completed correctly and that entries can be verified by source data. The CRF has to be filled out according to the specified CRF Completion Guidelines.

## **11.2 Data Handling**

Data entries undergo an automatic online check for plausibility and consistency. In case of implausibility, 'warnings' are produced. A responsible investigator is obliged either to correct the implausible data or to confirm its authenticity, and to give appropriate explanation. If not corrected, the data is flagged, enabling a convenient check of all questionable entries. A responsible monitor checks all flagged data and generates questions that are sent back to the responsible investigator. The investigator has to resolve all 'discrepancies'.

Further checks for plausibility, consistency, and completeness of data are performed after completion of the study. Queries are generated on the basis of these checks, combined with a visual control by a responsible monitor/data manager.

All missing data or inconsistencies are reported back to the sites and clarified by the responsible investigator. If no further corrections are to be made in the trial database it is declared closed and used for statistical analysis.

All data management activities are done according to the current Standard Operating Procedures (SOPs) of the IMBI.

## **11.3 Storage and Archiving of Data**

According to §13 of the German GCP-Regulation all important trial documents (e.g. CRFs) will be archived for at least 10 years after the trial termination. Responsible for archiving TMF including protocol, CRFs and reports is the CI.

The investigator(s) will archive all trial data (source data and Investigator Site File (ISF) including Patient Identification List and relevant correspondence) according to the section 4.9 of the ICH Consolidated Guideline on GCP (E6) and to local law or regulations. The Patient Identification List will be archived for at least 15 years after trial termination.

If the investigator relocates, retires, or for any reason withdraws from the study, the Sponsor should be prospectively notified. The study records must be transferred to an acceptable designee, such as another investigator, another institution, or to the Sponsor. The investigator must obtain Sponsor's written permission before disposing of any records, even if archiving requirements have been met.

# **12 Ethical and Legal Aspects**

## **12.1 Good Clinical Practice**

The procedures set out in this trial protocol, pertaining to the conduct, evaluation, and documentation of this trial, are designed to ensure that all persons involved in the trial abide by Good Clinical Practice (ICH-GCP E6 (R2)) and the ethical principles described in the current version of the Declaration of Helsinki. The trial is carried out in keeping with local legal and regulatory requirements.

## ***12.2 Patient Information and Informed Consent***

Before being admitted to the clinical trial, the patient must consent in written form to participate after the nature, scope, and possible consequences of the clinical trial have been explained in a form understandable to him or her. The original personally signed and dated Informed Consent Form must be kept on file by the investigator(s), and documented in the case report form.

A copy of the signed informed consent document must be given to the patient. The documents must be in a language easily understandable to the patient and must clearly state who informed the patient, which is confirmed by the dated signature of the responsible investigator.

If new safety information results in significant changes in the risk/benefit assessment, or if changes are made in the protocol, the consent form should be reviewed and updated if necessary. All patients (including those already being treated) should be informed of the new information and must give their written informed consent to continue the study.

## ***12.3 Confidentiality***

The data obtained in the course of the trial is treated pursuant to the applicable Data Protection Law (EU General Data Protection Regulation – GDPR - 2016/679), the Federal Data Protection Act (Bundesdatenschutzgesetz, BDSG), the State Data Protection Act of Baden-Württemberg (Landesdatenschutzgesetz, LDSG BW) as well as § 40 (2a) AMG.

During the clinical trial, patients are identified solely by means of an individual identification code (Patient ID). Storage of trial findings on a computer are done in accordance with local data protection law and are handled in strictest confidence. For protection of these data, organizational procedures are implemented to prevent distribution of data to unauthorized persons. The appropriate regulations of local data legislation are fulfilled in its entirety.

The patient consents in writing to relieve the investigator from his/her professional discretion in so far as to allow inspection of original data for monitoring purposes by health authorities and authorized persons (inspectors, monitors, auditors). Authorized persons (clinical monitors, auditors, inspectors) may inspect the patient-related data collected during the trial, ensuring the data protection law.

The investigator maintains a patient identification list (Patient IDs with the corresponding patient names) to enable records to be identified.

Patients who did not consent to circulate their pseudonymized data are not included into the trial.

## ***12.4 Responsibilities of Investigator***

The Principal Investigator should ensure that all persons assisting with the trial are adequately informed about the protocol and any amendments, the trial treatments, and their trial-related duties and functions.

The Principal Investigator should maintain a list of investigators and other appropriately qualified persons to whom he or she has delegated significant trial-related duties (Log of Staff).

The investigator(s) should support monitoring, auditing and inspections as described in sections 14.1 and 14.2.

## ***12.5 Approval of Trial Protocol and Amendments***

Before the start of the trial, the trial protocol, informed consent document, and any other appropriate documents are submitted to the independent Ethics Committee (EC) as well as to the competent authority. A written favorable vote of the EC and an (implicit) approval by the competent authority are a prerequisite for initiation of the clinical trial. The statement of EC should contain the title of the trial, the trial code, the trial site, and a list of reviewed

documents. It must mention the date on which the decision was made and must be officially signed by a committee member.

Before the first patient is enrolled in the trial, all ethical and legal requirements must be met. All planned substantial changes (see §10, (1) of German GCP-Ordinance) are submitted to EC and the competent authority in writing as amendments. They have to be approved by the EC and the competent authority.

The Coordinating Investigator or the NCT Trial Center, and if applicable the investigator(s) keep a record of all communication with the EC and the regulatory authorities.

